## Protocol Version History

| Version Number | Date | Protocol Update Finalised By
(insert name of person): | Reasons for Update |
|----------------|------|----------------------------------------------------------|--------------------|
|                |      |                                                          |                    |
|                |      |                                                          |                    |
|                |      |                                                          |                    |
|                |      |                                                          |                    |

## List of Abbreviations

|            |                                                                          |
|------------|--------------------------------------------------------------------------|
| ADL        | Activities in Daily Life                                                 |
| AE         | Adverse Event                                                            |
| ALI        | Acute Lung Injury                                                        |
| APR        | Annual Progress Report                                                   |
| AR         | Adverse Reaction                                                         |
| ARDS       | Acute Respiratory Distress Syndrome                                      |
| BBB        | Blood-brain barrier                                                      |
| BP         | Blood Pressure                                                           |
| CA         | Competent Authority                                                      |
| CI         | Chief Investigator                                                       |
| CNS        | Central Nervous System                                                   |
| COMT       | Catechol-O-methyltransferase                                             |
| CRF        | Case Report Form                                                         |
| CSF        | Cerebrospinal Fluid                                                      |
| CTA        | Clinical Trial Authorisation                                             |
| CTCAE      | Common Terminology Criteria for Adverse Events                           |
| CTIMP      | Clinical Trial of Investigational Medicinal Product                      |
| DIBD       | Developmental International Birth Date                                   |
| DDC        | Decarboxylase                                                            |
| DMC        | Data Monitoring Committee                                                |
| DSUR       | Development Safety Update Report                                         |
| EC         | European Commission                                                      |
| ECG        | Electrocardiogram                                                        |
| ELISA      | Enzyme-linked Immunosorbent Assay                                        |
| EMA        | European Medicines Agency                                                |
| EU         | European Union                                                           |
| EudraCT    | European Clinical Trials Database                                        |
| FDA        | Food and Drug Administration                                             |
| FSH        | Follicle Stimulating Hormone                                             |
| FPFV       | First Participant First Visit                                            |
| GBA | Gaucher gene                                                             |
| GCase      | Glucocerebrosidase                                                       |
| GCP        | Good Clinical Practice                                                   |
| GD         | Gaucher Disease                                                          |
| HED        | Human Equivalent Dose                                                    |
| HR         | Heart Rate                                                               |
| HPLC       | High Performance Liquid Chromatography                                   |
| HTA        | Human Tissue Authority                                                   |
| ICF        | Informed Consent Form                                                    |
| IgA        | Immunoglobulin A                                                         |
| IMP        | Investigational Medicinal Product                                        |
| ISF        | Investigator Site File                                                   |
| ITU        | Intensive Therapy Unit                                                   |
| LGC        | Laboratory of the Government Chemist                                     |
| L-DOPA     | Levodopa                                                                 |
| LP         | Lumbar Puncture                                                          |
| LPLV       | Last Participant Last Visit                                              |
| LWENC CRF  | Leonard Wolfson Experimental Neurology Centre Clinical Research Facility |

|           |                                                                                                    |
|-----------|----------------------------------------------------------------------------------------------------|
| MA        | Marketing Authorisation                                                                            |
| MAO-B     | Monoamine Oxidase B (MAO-B)                                                                        |
| MDS-UPDRS | Movement Disorder Society (MDS-sponsored) revision of the Unified Parkinson's Disease Rating Scale |
| MoCA      | Montreal Cognitive Assessment                                                                      |
| MHRA      | Medicines and Healthcare products Regulatory Agency                                                |
| NHNN      | National Hospital for Neurology and Neurosurgery                                                   |
| NHS R&D   | National Health Service Research & Development                                                     |
| NMSS      | Parkinson's Disease Non Motor Symptom Scale                                                        |
| NMS Quest | Parkinson's Non Motor Symptom Questionnaire                                                        |
| NOAEL     | No-observed-adverse-effect-level                                                                   |
| PD        | Parkinson disease                                                                                  |
| PI        | Principal Investigator                                                                             |
| PIC       | Participant Identification Centre                                                                  |
| PIS       | Participant Information Sheet                                                                      |
| PR        | Pulse Rate                                                                                         |
| QA        | Quality Assurance                                                                                  |
| QC        | Quality Control                                                                                    |
| QP        | Qualified Person                                                                                   |
| R&D       | Research & Development                                                                             |
| REC       | Research Ethics Committee                                                                          |
| RFH       | Royal Free London NHS Foundation Trust (Royal Free Hospital)                                       |
| RR        | Respiratory Rate                                                                                   |
| SAR       | Serious Adverse Reaction                                                                           |
| SAE       | Serious Adverse Event                                                                              |
| SAP       | Statistical Analysis Plan                                                                          |
| SDV       | Source Document Verification                                                                       |
| SoDA      | Summary of Drug Arrangements                                                                       |
| SOP       | Standard Operating Procedures                                                                      |
| SmPC      | Summary of Product Characteristics                                                                 |
| SSA       | Site Specific Assessment                                                                           |
| SSRIS     | Selective Serotonin Uptake Inhibitors                                                              |
| SUSAR     | Suspected Unexpected Serious Adverse Reaction                                                      |
| T         | Temperature                                                                                        |
| TID       | ter in diē (three times a day)                                                                     |
| TMF       | Trial Master File                                                                                  |
| TMG       | Trial Management Group                                                                             |
| TNFα      | Tumour Necrosis Factor alpha                                                                       |
| UCLH      | University College London Hospitals NHS Foundation Trust                                           |
| UCL       | University College London                                                                          |

## 1. Summary

This is a proof of concept investigational medicinal product (IMP) study to investigate the safety, tolerability and pharmacodynamic effects of the Glucocerebrosidase (GCase) enhancing chaperone ambroxol in Parkinson disease (PD) participants with and without Gaucher gene (*GBA*) mutations. Twenty participants will be recruited in total, 10 with a *GBA* positive status and 10 with a *GBA* negative status. Each participant will orally self-administer ambroxol (ambrosan) at 5 intra-participant dose escalations at 60 mg TID (day 1-7), 120 mg TID (day 8-14), 180 mg TID (day 15-28), 300 mg TID (day 22-28) and 420 mg TID (day 29-186).

Participants will be subjected to clinical and laboratory assessments to assess the safety, tolerability and pharmacodynamic effects of ambroxol on blood and CSF biomarkers. Lumbar punctures will be performed to assess the penetration of ambroxol into the cerebrospinal fluid (CSF) through the blood-brain barrier (BBB) in the central nervous system (CNS) and the effects of ambroxol on GCase activity. Biomarkers and GCase activity markers will be assessed through the visits.

Each participant will undergo 7 hospital visits and up to 12 telephone visits. Hospital visits will include 2 screening appointments within 60 days of the Day 1 hospital visit (at which participants will receive the first dose of ambroxol), followed by a visit within 3 days of the second dose escalation, Day 93 (month 3), Day 186 (month 6) and an end of study follow up/early termination visit at Day 279 (month 9). Participants will receive a telephone call to record any adverse events in between hospital visits after screening visit 2, visit 3, the first dose, between 1-3 days before and after each dose escalation (day 1, 8, 15, 22 and 29), between day 93 and day 186, between day 186 and day 279 and a final telephone call within 5 days of the day 279 hospital visit if an optional lumbar puncture (LP) is undertaken. Please refer to Appendix 1 for the detailed schedule of events.

## 2. Background and Rationale

PD is the second most common neurodegenerative disease after Alzheimer's disease with a prevalence of around 0.1% (Hobson et al., 2005; Schrag et al., 2000). The current lifetime risk for PD in the UK is estimated at 4% (Schapira et al., 2014). There is currently no therapy to slow down the progression in PD. Numerically the most important risk factor for the development of PD is the presence of the *GBA* mutation (Sidransky and Lopez, 2012).

GCase is a lysosomal hydrolase enzyme responsible for the degradation of the sphingolipid (class of lipids containing a backbone of sphingoid bases, a set of aliphatic amino alcohols that includes sphingosine) waste product glucosylceramide. Inherited mutations of *GBA* in the homozygous state cause Gaucher disease (GD), a lysosomal storage disorder in which the GCase substrate glucosylceramide accumulates in visceral organs, with a variety of clinical phenotypes (Grabowski, 2008). A mutation in the *GBA* gene in the heterozygous state represents carrier status that until recently was thought to be asymptomatic. It is presently estimated that approximately 7-10% of UK PD patients have *GBA* mutations and a mutation in heterozygous or homozygous form increases the risk of PD 20-30 fold (McNeill et al., 2012; Neumann et al., 2009; Sidransky et al., 2009; Winder-Rhodes et al., 2013). Penetrance of the PD phenotype amongst *GBA* carriers

(homozygous and heterozygous) is approximately between 10-30%. (Anheim et al., 2012; McNeill et al., 2012; Sidransky and Hart, 2012).

Idiopathic *GBA*-negative PD and *GBA*-positive PD are indistinguishable clinically, pharmacologically and pathologically except *GBA*-positive PD has a slightly earlier age of onset and a small increase in the frequency of age-adjusted cognitive impairment (Alcalay et al., 2012; Chahine et al., 2013; Setó-Salvia et al., 2012). The mechanisms by which *GBA* mutations result in PD are not yet understood, however there is evidence that it may be connected with reduced levels of GCase enzyme activity. For instance, transgenic mice carrying mutations associated with PD and idiopathic PD brains/CSF appear to demonstrate reduced GCase activity (Gegg et al., 2012; Parnetti et al., 2014; Sardi et al., 2013). Furthermore, it has been demonstrated that there is a reciprocal relationship between GCase activity and levels of alpha synuclein, the cytosolic protein which is the main constituent of Lewy bodies, the pathological hallmark of PD (Cullen et al., 2011; Mazzulli et al., 2011). Alpha synuclein has also been shown directly to interact with *GBA in vitro*, an interaction which is reduced in mutant forms of the protein (Yap et al., 2013a; Yap et al., 2013b). There is evidence from cell and animal models that there is a reciprocal relationship between GCase and alpha-synuclein (Schapira and Gegg, 2013). Thus, elevation of GCase activity reduces alpha-synuclein levels and increased alpha-synuclein lowers GCase activity. This has raised the possibility that modulation of GCase enzyme activity may represent a putative neuroprotective mechanism in PD.

Current treatment for patients with GD includes enzyme replacement therapy however this treatment does not cross the BBB, making it unsuitable as for a CNS condition such as PD. There is extensive research on the use of pharmacological chaperones to enhance lysosomal *GBA* activity (Parenti, 2009). Screening of a library of 1,040 Food and Drug Administration (FDA) approved drugs identified ambroxol, a respiratory decongestant (which is a surfactant stimulant, a mucokinetic and secretagogue) as a potential chaperone for *GBA*. Our laboratory has confirmed that ambroxol has a distinct mode of action which enhances GCase activity in human *GBA* fibroblasts (McNeill et al., 2014).

Ambroxol hydrochloride appears to facilitate the refolding of misfolded mutant *GBA* protein at the endoplasmic reticulum, allowing effective trafficking to the lysosome (Bendikov-Bar et al., 2013; Westbroek et al., 2011). Preliminary *in vivo* studies from our own laboratory have confirmed ambroxol administration is able to increase GCase activity levels within mouse brains. The proposed design is a proof of principle trial to demonstrate that ambroxol is able to reach the CNS and increase GCase activity in human CSF. If confirmed, it will pave the way for a larger phase III trial to test clinically and biochemically the neuroprotective effect of ambroxol in *GBA*-positive and idiopathic *GBA*-negative PD. If positive, this would represent the first neuroprotective treatment in PD to date.

## 2.1 Ambroxol Justification of Route of Administration and Dosage

Ambroxol (brand name: ambrosan) has a long history of use in humans, which documents its very low level of toxicity. For several decades now ambroxol has held market authorisation (MA) by the European Medicines Agency (EMA) and in several countries across Europe for over-the-counter indications at doses up to 120 mg/day. There have been a number of clinical trials of ambroxol at a variety of doses. In one small study 12 participants with type I GD took 150 mg daily in two divided doses for 6 months with minimal side effects. This study showed some improvement in clinical features of GD, particularly in those with the lowest weight. Briefly, all but one participant experienced an increase in their platelet count (average 11.8% increase) and all but two experienced a reduction in splenic volume (average 2.7% reduction), both positive features in GD (Zimran et al., 2013). A recent study in Japan treated 5 neuronopathic GD patients with ambroxol at an escalating dose of 3mg/kg/day to 5mg/kg/dose for 12-31 months. (Narita et al., 2013). The study reported anecdotal improvements in myoclonus and seizure frequency. The only adverse event reported was mild hyperuricaemia (Narita et al., 2016). Another study treated 12 healthy volunteers with 500 mg or 1g twice a day for 5 days and revealed no adverse effects (Oosterhuis et al., 1993). A number of studies have demonstrated use of a 1g daily dose on (Intensive Therapy Unit) ITU in participants with acute respiratory distress syndrome (ARDS) for short periods. In one study 32 participants with Acute Respiratory Distress Syndrome (ARDS) were administered 40 mg/kg ambroxol in 4 daily divided doses for up to 10 days with no adverse effects (Baranwal et al., 2015) whilst a recent meta-analysis of 508 participants enrolled in studies using high dose ambroxol (15-20mg/kg/day) for short periods (3-7 days) to treat ARDS and acute lung injury (ALI) did not reveal any significant adverse effects (Wu et al., 2014). A further trial assesses the efficacy of ambroxol (1g dose administered every 12 hours for a maximum of 48 hours) prophylactically in pregnant women to prevent infantile ARDS. The study demonstrated its safety to pregnant woman and the unborn child (Visani and Daniotti, 1992). Pre-clinically, the oral administration of ambroxol in GD mice has demonstrated its wide distribution and chaperone activity in tissues, including the brain, and lack of acute toxicity (Luan et al., 2013).

Ambroxol has a low index for acute toxicity. No toxicological effect on target organs has been detected to date. Four week intravenous toxicity studies with ambroxol in rats (4, 16 and 64 mg/kg/day) and in dogs (45, 90 and 120 mg/kg/day (infusion 3 h/day) showed no severe local or systemic toxicity including at histopathology. All adverse effects were reversible. Ambroxol was neither embryotoxic nor teratogenic when tested at oral doses up to 3000 mg/kg/day in rats and up to 200 mg/kg/day in rabbits. The fertility of male and female rats was not affected up to 500 mg/kg/day. Genotoxicity studies in vitro (Ames and chromosome aberration test) and in vivo (mouse micronucleus test) did not reveal any mutagenic potential of ambroxol. Ambroxol did not show any tumorigenic potential in carcinogenicity studies in mice (50, 200 and 800 mg/kg/day) and rats (65, 250 & 1000 mg/kg/day) when treated with a dietary admixture for 105 and 116 weeks, respectively.

The Human Equivalent Dose (HED) based on the no-observed-adverse-effect-level (NOAEL) derived allometric scaling of animal pharmacokinetics to human exposure was: 150 mg/kg/day in mice (following 4 weeks treatment), corresponding to a HED of 12.1 mg/kg; 50 mg/kg/day in rats (52 and 78 weeks), corresponding to a HED of 8.0 mg/kg; 40 mg/kg in rabbits (26 weeks), corresponding to a HED of 12.9 mg/kg; 10 mg/kg in dogs (52 weeks), corresponding to a HED of 5.5 mg/kg). The above NOAELs together

with the available clinical doses tested in humans provide toxicity cover for the dose chosen in this study at 5 intra-participant dose escalations at 60 mg TID (day 1-7), 120 mg TID (day 8-14), 180 mg TID (day 15-28), 300 mg TID (day 22-28) and 420 mg TID (day 29-186).

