## **2.2 Scientific Rationale for Ambroxol 1260 mg TID maximum dose**

To date, ambroxol has been used as an over-the-counter cough linctus for peripheral effects on respiratory mucosa. It has obtained market authorisations in a number of European markets. It has been shown in a number of studies to be safe for long term administration (Narita et al., 2016 & Zimran et al., 2013). This includes the study of Narita et al., 2016 where participants were given ambroxol in excess (up to 1.3 g total daily dose) of the maximum dose of 1.26g total daily dose proposed in our protocol, and for periods of up to 4 years. A number of other studies have used a total daily dose in excess of 1g for up to 10 days including one in the third trimester of pregnancy (Wu et al., 2014 & Baranwal et al., 2015).

The scientific basis for the use of ambroxol in PD has been established with a number of mechanistic studies (see above). CNS penetration has been confirmed by increased glucocerebrosidase activity and protein levels in animal studies using rodents and 5mM ambroxol in drinking water, available *ad libitum*. A limited non-human primate study was performed using 22.5 or 100 mg/day ambroxol by gavage for 28 days. Brain glucocerebrosidase was increased with the 100 mg but not the 22.5 mg dose. On an mg/kg basis, these doses correspond to 4.5 mg/kg/day and 20 mg/kg/day respectively in the non-human primates, approximately equivalent to 315 mg/day and 1400 mg/day in humans. These data are currently in submission for publication.

Narita et al studied the effects of ambroxol in 5 patients with Gaucher disease (homozygous glucocerebrosidase mutations) with daily doses of 1200 mg for 4 years, 1200 mg for 3 years, 1300 mg for 3 years, 625 mg for 0.5 years and 375 mg for 2 years and measured serum and CSF ambroxol concentrations and substrate (glucosylsphingosine) levels over these periods. No significant adverse events were noted. Ambroxol was detectable at 0.06-0.83uM/L in CSF, these levels are anticipated to be detectable in our assays, but the lower range is at the limit of detection. There was a reduction in substrate levels indicating enhanced glucocerebrosidase activity in the CSF, although this was not measured.

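### At the implied 70 kg, the top dose step exceeds all four NOAEL-derived human equivalent doses cited as cover in section 2.1, and section 2.2 summarises long-term human exposure more favourably than it lists it

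*Protocol*

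**What the plan says.** Section 2.1 gives four NOAELs with their HEDs: mice 12.1 mg/kg (4 weeks), rats 8.0 mg/kg (52 and 78 weeks), then "40 mg/kg in rabbits (26 weeks), corresponding to a HED of 12.9 mg/kg" and "10 mg/kg in dogs (52 weeks), corresponding to a HED of 5.5 mg/kg". It concludes that these NOAELs, taken "with the available clinical doses tested in humans provide toxicity cover for the dose chosen in this study", support the whole five-step escalation.

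Section 2.2 says that participants in a Gaucher study received ambroxol "in excess (up to 1.3 g total daily dose) of the maximum dose of 1.26g total daily dose proposed in our protocol", for as long as 4 years. It then lists the five patients. Four are given as "1200 mg for 4 years, 1200 mg for 3 years, 1300 mg for 3 years, 625 mg for 0.5 years"; the fifth patient's daily dose was 375 mg, over 2 years. The same section converts primate doses of 4.5 and 20 mg/kg/day to amounts "approximately equivalent to 315 mg/day and 1400 mg/day in humans".

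Section 3 classifies the trial as Type B, somewhat above the risk of standard care, on the strength of the information that precedes it.

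Three passages on dosing do not agree with the rest of the protocol or with themselves:
- Sections 1 and 2.1 give "180 mg TID (day 15-28), 300 mg TID (day 22-28", so two steps share days 22-28. The other sections put 180 mg TID on days 15-21.
- The heading of 2.2 reads "Scientific Rationale for Ambroxol 1260 mg TID maximum dose", while the dosing table in 10.7 gives 420 mg TID, 1260 mg/day.
- Section 10.8 first says that a missed dose is taken once the participant notices it. It then says that the participant goes on to the next dose of that day.

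**The concern.** An HED derived from a NOAEL supports a human dose when the dose lies at or below it. Section 2.1 places the HEDs next to its conclusion without converting the planned dose to the same unit, so a reader cannot see on which side of them the top step falls. If it falls above, the animal part of the argument does not support that step, and the human data must do so alone.

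The description of the human data then matters more. The top step lasts 158 days, so long-term exposure is the relevant comparison. A summary that joins the highest dose in one patient to the longest duration in another makes that exposure look larger than it was.

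The stake is the accuracy of the safety statement on which the risk classification draws, and on which the patient information may draw. The missed-dose text is a separate matter with a practical side, because participants take the tablets themselves at home.

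**Working it through.** **Inputs.** Top dose: 420 mg TID on days 29-186 (10.7). HEDs: 12.1, 8.0, 12.9 and 5.5 mg/kg (2.1), read as daily doses. Body weight: no reference weight is stated, so it is taken from the conversion in 2.2.

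**Reproducing the plan's own figures.**
- Daily dose: 3 × 420 = 1260 mg. This agrees with 10.7.
- Implied weight: 315 / 4.5 = 70 kg and 1400 / 20 = 70 kg. Both conversions in 2.2 use 70 kg.
- Days at the top step: 186 − 29 + 1 = 158.

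**Top step against the HEDs.** 1260 / 70 = 18.0 mg/kg/day. Break-even weight = 1260 / HED.

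| Species | HED, mg/kg | HED × 70 kg, mg/day | 18 / HED | Break-even weight, kg |
|---|---|---|---|---|
| Rabbit | 12.9 | 903 | 1.40 | 97.7 |
| Mouse | 12.1 | 847 | 1.49 | 104.1 |
| Rat | 8.0 | 560 | 2.25 | 157.5 |
| Dog | 5.5 | 385 | 3.27 | 229.1 |

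**Sensitivity to weight.** The top step is 25.2 mg/kg/day at 50 kg, 21.0 at 60, 15.75 at 80, 14.0 at 90 and 12.6 at 100. Below 97.7 kg it exceeds all four HEDs. At 100 kg it is under the rabbit HED only.

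**All five steps at 70 kg.**

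| Step | mg/day | mg/kg/day | Position against the HEDs |
|---|---|---|---|
| 1 | 180 | 2.57 | below all four |
| 2 | 360 | 5.14 | below all four |
| 3 | 540 | 7.71 | above dog, below the other three |
| 4 | 900 | 12.86 | below rabbit only |
| 5 | 1260 | 18.0 | above all four |

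**Long-term human exposure, total mg/day, from the list in 2.2.**

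| Patient | Dose, mg/day | Duration, years | Above 1260? |
|---|---|---|---|
| 1 | 1200 | 4 | no |
| 2 | 1200 | 3 | no |
| 3 | 1300 | 3 | yes, by 40 mg (3.2%) |
| 4 | 625 | 0.5 | no |
| 5 | 375 | 2 | no |

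One of five exceeded 1260 mg/day, and that patient was treated for 3 years. Nobody exceeded it for 4 years. The other long-term study in 2.1 used 150 mg/day in 12 patients for 6 months. The patients' weights are not given, so this count cannot be repeated in mg/kg.

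**Short-term human exposure (2.1).** 40 mg/kg for up to 10 days in 32 participants; 15-20 mg/kg/day for 3-7 days in a meta-analysis of 508; up to 2 g/day for 5 days in a study of 12 volunteers. These reach or pass 18 mg/kg/day or 1260 mg/day, but for 10 days at most against 158.

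**Dosing text.** The overlap in sections 1 and 2.1 covers 7 days (22-28). The heading of 2.2, read literally, is 3 × 1260 = 3780 mg/day, three times the dosing table. In 10.8, a participant who notices in the early afternoon that the morning dose was missed would take it under the first sentence and leave it out under the second.

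**The case against.** The strongest reply is that 2.1 makes a joint claim, from the NOAELs together with the human doses, and that testing the animal half alone is unfair. This stands in part. Short-term human doses at or above the top step are cited, in several hundred participants, without significant adverse effects. Section 2.1 also reports four-week intravenous studies in dogs up to 120 mg/kg/day without severe toxicity, and negative carcinogenicity studies at far higher doses. Those animal studies are not presented as NOAELs, however, and no HED is given for them. The concluding sentence relies on the NOAELs, and at the top step they point the other way.

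A reader might infer that the NOAELs give no cover at all. The figures do not support that: steps 1 and 2 are below every HED, and steps 3 and 4 below at least one.

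On the Gaucher patients, it can fairly be said that 2.2 states two maxima and then lists every patient, so nothing is hidden, and that 1200 mg is only about 5% below 1260 mg. That limits the harm. The summary still does not match the list.

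A reader might also fault the protocol for scaling the primate effect by plain mg/kg and toxicity allometrically. Section 2.2 says openly that its conversion is on a mg/kg basis and approximate, so a common basis would be a preference and its absence is not an error.

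The practical consequences should not be overstated. Section 2.2 attributes the escalation, visits, calls and safety tests to anaphylaxis reports and to unreported or idiosyncratic effects, not to a NOAEL margin, and section 3 already rates the risk above standard care. The patient information is not shown, so an effect on consent cannot be checked. The day overlap and the heading are slips: the synopsis, 4.1, 5.1, 6.3, 7.3, 9.10, 10.7 and Appendix 1 agree on days 15-21, and the text below the heading gives 1.26 g as the daily total.

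**Conclusion.** The point holds for the top step and for the summary of long-term exposure. At 70 kg, 1260 mg/day is 1.4 to 3.3 times the four HEDs, and it is above all four at any weight under 97.7 kg. Cover for days 29-186 therefore rests on human data: short courses of up to 10 days at or above this dose, five Gaucher patients of whom one exceeded 1260 mg/day (3 years) and two took 1200 mg/day (3 and 4 years), and 12 patients at 150 mg/day.

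The assumptions are the 70 kg implied by 2.2, the HEDs read as daily doses, and a comparison of the Gaucher patients in total mg.

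A reader might go further and conclude that the dose is unsafe. The documents do not show this. Exceeding a NOAEL-derived HED means that the animal data do not supply a margin, not that harm is expected, and no significant adverse events are reported in the cited patients. What is wrong is the stated margin.

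The two sentences of 10.8 conflict in an operative instruction. The day range and the heading are editorial conflicts that other sections contradict. The arithmetic is certain; the effect on risk assessment and consent is less so.

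**What to change.** - In 2.1 and 2.2, state that at 70 kg the top step is 1.4 to 3.3 times the NOAEL-derived HEDs, that steps 1 and 2 lie below all four, and that cover for the top step rests on the human data.
- In 2.2, replace the summary of the Gaucher study with the exposure as listed: one patient above 1260 mg/day for 3 years, two at 1200 mg/day for 3 and 4 years, two at lower doses, weights not given. Keep the short-term studies and state their durations beside them.
- Re-read the section 3 risk classification and the patient information against the corrected statement.
- Reconcile the two missed-dose sentences of 10.8, the days 15-28 in sections 1 and 2.1 with the days 15-21 elsewhere, and the heading of 2.2 (also in the contents list) with the dosing table. Which dose, day range or rule is right is for the sponsor and the investigator to decide, and no view is taken here.

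The cost is a text amendment with whatever approval section 15 requires, and one review of the risk classification and patient information. The stated safety margin becomes less favourable. Design, sample size and analysis are unaffected.
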